## Abstract

**Background::**

Hepatocellular carcinoma (HCC) is one of the most common type of malignant tumors in adults, and is the most common cause of death in people with cirrhosis. Both laparoscopic hepatectomy (LH) and radiofrequency ablation (RFA) are radical treatments for small HCC. However, there is no international standard for the treatment of small HCC, and it is still controversial to choose LH or RFA in treating small HCC. We try to carry out a randomized, controlled, prospective study to compare the the short-term and long-term effects and safety of LH versus RFA in the treatment of small HCC.

**Methods::**

This study is a single-center, evaluator-blinded, randomized, controlled clinical trial (RCT). The patients will be randomly divided into RFA group and LH group in a 1:1 ratio according to a computer-generated randomization list. Postoperative complications rates, Alpha fetoprotein (AFP), hospital stay, 1, 2, 3-year overall survival (OS) rates, disease-free survival (DFS) rates and all possible adverse events will be recorded. Statistical analyses will be performed with SPSS v22.0 software.

**Conclusions::**

The study will compare the the short-term and long-term effects and safety of LH versus RFA in the treatment of small HCC.

**OSF Registration number::**

doi: 10.17605/OSF.IO/HNX2T

## Introduction

1

Hepatocellular carcinoma (HCC) is one of the most common type of malignant tumors in adults, and is the most common cause of death in people with cirrhosis.^[1,2]^ The vast majority of HCC occurs in Asia and sub-Saharan A, especially in China, with an incidence rate of 21.35 per 100,000 and a case fatality rate of 18.43 per 100,000.^[3]^ It occurs in the setting of chronic liver inflammation, and is mainly related to hepatitis B virus infection, liver cirrhosis, or exposure to alcohol or aflatoxin.^[4]^ Small HCC refers to a single cancer nodule with a maximum diameter of ≤3 cm or two nodules with a combined diameter of ≤3 cm, without obvious symptoms and signs.

Surgical resection is associated with better cancer prognosis. The conventional open hepatectomy is associated with more blood loss, longer recovery time, high incidence of complication and mortality.^[5]^ With the improvement of laparoscopy technology, laparoscopic hepatectomy (LH) has been widely used in treating resectable HCC, with satisfactory short-term and long-term outcomes.^[6–8]^ However, less than 30% of patients with small HCC are eligible for surgery,^[9]^ due to many factors such as extrahepatic metastasis, vascular invasion, high-risk anatomical locations, excessive lesions, and insufficient liver to sustain life. Therefore, many non-surgical alternatives have been developed, including radiofrequency ablation (RFA). RFA has been established as the standard of care for patients with small HCC unsuitable for surgical resection. A large number of studies have shown that it is safe, effective, minimally invasive, with minimal complication and mortality.^[10–12]^

Both LH and RFA are radical treatments for small HCC. However, there is no international standard for the treatment of small HCC, and it is still controversial to choose LH or RFA in treating small HCC.^[13]^ Though RFA in safer than LH, the recurrence rate and local lesion progression rate are higher,^[14]^ which made LH the preferred treatment for HCC. Therefore, we try to carry out a randomized, controlled, prospective study to compare the the short-term and long-term effects and safety of LH versus RFA in the treatment of small HCC.

## Method

2

### Study design

2.1

This study is a single-center, evaluator-blinded, randomized, controlled clinical trial (RCT), which has been registered in in open science framework (OSF) (Registration number: doi: 10.17605/OSF.IO/HNX2T). The protocol was approved by the Ethics Committee of The Ninth People's Hospital of Chongqing, and it will be carried out in accordance with the Declaration of Helsinki. The study protocol conforms to the Standard Protocol Recommendations for Interventional Trials (SPIRIT) 2013 Statement,^[15]^ and the results will be reported according to the CONSORT Statement extension for trials^[16]^ (Fig. 1).

**Figure 1 F1:**
[figure not shown]
Flow diagram.

### Participants

2.2

#### Sample size

2.2.1

Patients meeting the inclusion and exclusion criteria will be mainly recruited from inpatients of the Department of General Surgery, The Ninth People's Hospital of Chongqing.

According to the previous report, the 3-Year survival rate of small HCC is 70%, taking α = 0.05 and 1-β = 0.8, 355 samples will be needed in each group. Considering the withdrawal rate of 10%, the total number of patients is determined as 760, 380 in each group.

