### Statistical methods

2.5

Statistical analyses will be performed with SPSS v22.0 software (SPSS Inc., Chicago, IL). Statistical testing is two-sided and *P* < .05 is considered to be statistically significant. Considering the homogeneity, group *t* test for normally distributed data or Mann-Whitney *U* test for non-normally distributed data will be used to compare variables between groups. A Pearson Chi-square test was applied to analyze categorical data. All curves were generated by the Kaplan-Meier method and the differences between the groups were compared using the log-rank test.

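### The 10% withdrawal allowance in the sample size is miscalculated (380 per group instead of 395), and no difference is stated, so 355 per group and 80% power cannot be verified

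*Protocol article*

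**What the plan says.** Section 2.2.1 (Sample size) takes a 3-year survival rate of 70% for small HCC from an earlier report and does not assign it to either arm. It continues: "taking α = 0.05 and 1-β = 0.8, 355 samples will be needed in each group". The withdrawal step follows directly: "Considering the withdrawal rate of 10%, the total number of patients is determined as 760, 380 in each group".

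Section 2.5 (Statistical methods) settles the sidedness, which the sample-size text does not repeat: "Statistical testing is two-sided". The same section plans Kaplan-Meier curves with a log-rank comparison. Section 2.2.4 sets 1:1 allocation, and section 2.4.2 lists survival at 1, 2 and 3 years with visits every 3 months.

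No second survival rate, difference, hazard ratio or non-inferiority margin appears anywhere in the article.

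**The concern.** Two things do not hold together.

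- **The withdrawal step.** The number needed, the withdrawal rate and the number enrolled stand in adjacent sentences, and the third does not follow from the first two.
- **The base number.** A two-group comparison cannot be sized from one proportion. The text does not say how large a difference the 80% power refers to, or whether 70% is the better or the worse arm.

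This section is the article's only justification for enrolling 760 patients. As written, a reader cannot reproduce the enrolment figure from the inputs, and cannot tell which contrast between laparoscopic hepatectomy and radiofrequency ablation the trial was sized for.

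**Working it through.** **Inputs from the article.** 355 per group before withdrawal, 10% withdrawal, 380 per group (760 total), α = 0.05, power 0.80 and 70% survival at 3 years (all section 2.2.1); two-sided testing and the log-rank test (section 2.5); 1:1 allocation (section 2.2.4).

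**Step 1: trying to reproduce 380.**

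| Route | Calculation | Per group | Total |
|---|---|---|---|
| Correct inflation, n/(1 − d) | 355/0.9 = 394.4 | 395 | 790 |
| Common shortcut, n × (1 + d) | 355 × 1.1 = 390.5 | 391 | 782 |
| Stated | – | 380 | 760 |

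Neither route gives 380. The stated figure is 395 − 380 = 15 per group, or 30 in total, below the correct one. Working backwards, 380 × 0.9 = 342, which is 13 below 355, and 1 − 355/380 = 6.6% is the most withdrawal that 380 can absorb.

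**Step 2: trying to reproduce 355.** The second rate is missing, so this can only be a search. The formula is the two-sided, pooled two-proportion one:

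n = [1.96·√(2p̄(1 − p̄)) + 0.8416·√(p₁(1 − p₁) + p₂(1 − p₂))]² / (p₁ − p₂)²

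For 70% against 60%, p̄ = 0.65, and n = (1.3221 + 0.5646)²/0.01 = 355.9. With p₁ = 70% throughout:

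| Assumed second rate | n per group (rounded up) |
|---|---|
| 60% | 356 |
| 65% | 1,377 |
| 75% | 1,251 |
| about 79.1% | about 355 |
| 80% | 294 |

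So 355 fits a fall of about 10 points or a rise of about 9 points. Both second rates are back-calculated and are not figures in the document. Power depends heavily on this choice: with 342 per group, a 5-point difference has about 29% power (against 65%) or 31% (against 75%).

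**Step 3: what the withdrawal slip costs if 355 does give 80%.** Suppose withdrawn patients contribute nothing. Then power at 342 is approximately

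Φ[(1.96 + 0.8416)·√(342/355) − 1.96] = Φ(0.790) = 78.5%.

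The pooled formula, with the difference tuned so that 355 gives exactly 80%, also returns 78.5% in either direction. The loss is about 1.5 points.

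**Step 4: the same question under the planned log-rank test.** Assume 70% against 60%, exponential survival and 3 years of follow-up for those who do not withdraw. The hazard ratio is ln(0.6)/ln(0.7) = 1.432, with log 0.3592. With D deaths, power is Φ(√D/2 × 0.3592 − 1.96).

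- *Withdrawn patients contribute nothing:* D = 342 × (0.30 + 0.40) = 239.4, power 79.4%.
- *Withdrawals spread evenly over 3 years and censored:* a withdrawing patient dies on study before withdrawal with probability 1 − (1 − S)/(−ln S), which is 0.159 for S = 0.7 and 0.217 for S = 0.6. D = 342 × 0.30 + 38 × 0.159 + 342 × 0.40 + 38 × 0.217 = 253.7, power 81.6%.

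For comparison, 355 per group with complete follow-up gives 355 × 0.70 = 248.5 deaths. In the second case, 380 with 10% withdrawal yields slightly more deaths than that.

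**The case against.** A reader might infer that the trial is underpowered, or that the claimed 80% is shown to be missed. The document does not support this.

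- With no difference stated, the power is unverifiable, which is not the same as too low. Any figure below 80% rests on a second rate that the reviewer supplies, or on taking for granted that 355 gives 80%.
- The 78.5% discards every withdrawn patient. The planned log-rank test keeps such a patient until censoring, and with evenly spread withdrawals the power under 70% against 60% stays above 80%.
- Even in the worst case the slip costs about 1.5 points, with little effect on inference.

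All three stand, and they limit the conclusion.

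It can also be said that the missing second rate is an effect of condensation: the full protocol or the earlier report may give it. That is possible. But the article chose to present a derivation, and the inputs it prints cannot produce its result. Condensation does not explain the withdrawal step, where every input and the result are printed.

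Finally, a reader might infer that without a planning difference a null result could not be interpreted. That goes too far, because the confidence interval of the result shows which differences are excluded. What is lost is the ability to judge beforehand whether 760 is a sensible size.

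**Conclusion.** Two defects hold. First, the withdrawal allowance is an arithmetic error on the section's own figures. This needs no outside assumption. Second, the base of 355 and its 80% power are tied to no stated difference, so they can be neither confirmed nor refuted from the text.

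It is not established that the trial has less than 80% power. The 1.5-point loss is conditional on 355 being right and on withdrawn patients giving no information. The log-rank figures in turn assume 70% against 60%, exponential survival and a particular withdrawal pattern. The point is a needed correction to a headline figure and its basis, of modest consequence for inference, and not a reason to question the viability of the trial.

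**What to change.** Revise section 2.2.1 in two places.

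1. **State the difference.** The sponsor gives the second 3-year survival rate that produced 355, says which arm has it, and names the formula or test used. The reviewer's 60% or 79% should not be written in unless the sponsor confirms it.
2. **Correct the withdrawal statement.** Keeping 760, say either that 380 per group retains 355 with up to about 6.6% withdrawal, or that at 10% withdrawal 342 per group remain. In the latter case give the power: about 78.5% if 355 gives 80% and withdrawn patients contribute nothing, with the loss smaller or absent under the log-rank test with censoring. If the sponsor prefers to keep 355 after 10% withdrawal, the consistent figures are 395 per group and 790 in total.

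Keeping 760 costs only wording and no extra patients. The alternative adds 30 patients and is not needed to make the text correct.

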#### Inclusion criteria

2.2.2

Patients will be included if they meet the following inclusion criteria:

(1)Patients meeting the diagnostic criteria for HCC;(2)Child–Pugh class A or B;(3)Three or fewer tumors ≤ 3 cm in diameter;(4)No vascular invasion and no extrahepatic metastasis.(5)Written informed consent.

#### Exclusion criteria

2.2.3

Patients will be excluded with the following exclusion criteria:

(1)A total bilirubin ≥ 3.0 mg/dl;(2)Platelet count < 40,000/μl or prothrombin activity < 40%;(3)Decompensated liver cirrhosis, severe portal hypertension, history of bleeding from gastric fundus or esophageal varices, severe hypersplenism or refractory ascites;(4)Presence of other uncontrollable malignancie.

#### Randomization and blinding

2.2.4

The patients will be randomly divided into RFA group and LH group in a 1:1 ratio according to a computer-generated randomization list. Due to the limitation of treatment, the surgeons and patients are not blinded, and the statistical analysis will be carried out by an independent professional researcher who will not know the identification of the groups.

### Interventions

2.3

All patients will be admitted to the hospital, and general information such as age and gender will be recorded. Before the operation, blood routine test, liver and kidney function, blood glucose, coagulation electrocardiogram, chest X-ray examination, and abdominal ultrasound, colonoscopy, pathological biopsy, will be examined if necessary, to exclude surgical contraindications.

Patients in LH group will get the laparoscopic liver resection treatment in general anesthesia, and each operation is performed by a surgeon with 10 years or more experience in laparoscopic liver resection. Anti-inflammatory, acid suppression, liver protection, maintenance of internal environment stability and symptomatic treatment will be performed after the operation.

Patients in RFA group will be treated with percutaneous radiofrequency ablation with Cool-tip, RF Ablation System (COVIDIEN) in local anesthesia. During the ablation process, each patient is injected intravenously with mida saliva to relieve pain. Anti-inflammatory, acid suppression, liver protection, maintenance of internal environment stability and symptomatic treatment will be performed after the operation.

### Outcome variables

2.4

#### Short-term outcomes

2.4.1

(1)Postoperative complications rates, involving high fever, biliary tract injury, bleeding, abdominal infection;(2)Alpha fetoprotein (AFP) 2 months after operation;(3)Hospital stay: the interval from the date of initial treatment to discharge.

#### Long-term outcomes

2.4.2

(1)1, 2, 3-year overall survival (OS) rates;(2)1, 2, 3-year disease-free survival (DFS) rates;(3)Local recurrence rate.

Long-term outcomes will be recorded every 3 months during the follow-up visits to monitor survival rates and tumor recurrence. Follow-up visits will be closed at the time of death or the last visit of the patient.

#### Safety evaluation

2.4.3

All possible adverse events (AEs) will be recorded, such as bleeding, pain, urinary retention.

### Statistical methods

2.5

Statistical analyses will be performed with SPSS v22.0 software (SPSS Inc., Chicago, IL). Statistical testing is two-sided and *P* < .05 is considered to be statistically significant. Considering the homogeneity, group *t* test for normally distributed data or Mann-Whitney *U* test for non-normally distributed data will be used to compare variables between groups. A Pearson Chi-square test was applied to analyze categorical data. All curves were generated by the Kaplan-Meier method and the differences between the groups were compared using the log-rank test.

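### No outcome is named primary and every comparison is declared significant at P < .05, so the plan does not fix which result, or which test of survival, decides the trial

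*Protocol article*

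**What the plan says.** **Outcomes.** Section 2.4.1 lists three short-term outcomes. The first is "Postoperative complications rates, involving high fever, biliary tract injury, bleeding, abdominal infection", the second is "Alpha fetoprotein (AFP) 2 months after operation", and the third is hospital stay. Section 2.4.2 lists "1, 2, 3-year overall survival (OS) rates;(2)1, 2, 3-year disease-free survival (DFS) rates", followed by local recurrence. Section 2.4.3 adds the recording of adverse events. None of these is called primary or secondary there, in the abstract or anywhere else in the article. The stated aim covers short-term effects, long-term effects and safety together, without a lead question.

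**Sample size.** Section 2.2.1 starts from a single figure, "the 3-Year survival rate of small HCC is 70" per cent, and continues: "taking α = 0.05 and 1-β = 0.8, 355 samples will be needed in each group". It gives no survival rate for the other arm and no target difference.

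**Testing.** Section 2.5 states: "Statistical testing is two-sided and *P* < .05 is considered to be statistically significant". It assigns t or Mann-Whitney tests to continuous data, chi-square to categorical data, and Kaplan-Meier with log-rank to curves. It exempts, orders or adjusts none of these tests.

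**The concern.** A two-arm trial needs one result, fixed in advance, that answers its question. Here the sample size points to survival, but the outcome list and the significance rule do not follow it. Three-year OS stands beside 1- and 2-year OS without distinction, and section 2.5 gives every comparison its own 0.05.

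Two things are at stake. First, a conclusion could rest on whichever outcome or time point crosses .05. The 0.05 in the sample-size section describes one comparison, not the set of comparisons that section 2.5 allows.

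Second, the Introduction expects RFA to be safer than LH but to have more recurrence and local progression. On the protocol's own expectation, complications may favour one arm and DFS or recurrence the other, both below .05. The plan has no rule for which of these answers the trial's question.

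**Working it through.** **1. What the plan's own figure tells us.** Section 2.2.1 gives 70% survival at 3 years, α = 0.05, power 0.8 and 355 per group. The second rate is missing, so 355 cannot be derived from the document alone. Assuming 60% in the other arm, the pooled two-proportion formula gives

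n = [1.96·√(2·0.65·0.35) + 0.842·√(0.7·0.3 + 0.6·0.4)]² / 0.10² ≈ 356.

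The arcsine version gives 355.4 and the unpooled version 353.2. A log-rank calculation by Freedman's formula, with hazard ratio ln 0.6 / ln 0.7 = 1.43 and 249 deaths, gives 249 / (0.3 + 0.4) ≈ 356 per arm. Schoenfeld's formula (244 deaths) gives 349.

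So 355 fits one survival comparison at two-sided 0.05 under an assumed 70% versus 60%. It does not show whether that comparison is of 3-year rates or of curves, because both routes lead to nearly the same number.

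**2. How many tests.** The article does not fix the count.

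| Reading | Tests | Count |
|---|---|---|
| One log-rank test each for OS and DFS | complications, AFP, stay, OS, DFS, local recurrence | 6 |
| Each yearly rate tested | complications, AFP, stay, OS ×3, DFS ×3, local recurrence | 10 |

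Adverse-event comparisons are counted in neither.

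**3. Chance of at least one P < .05 when the treatments differ on no outcome.** For k independent tests this is 1 − 0.95^k:

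- k = 6: 1 − 0.95^6 = 26.5%
- k = 10: 1 − 0.95^10 = 40.1%

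**4. Allowing for correlation.** The documents give no correlations, so these are assumptions.

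- Ten equally correlated tests (400,000 simulated draws): 37.7% at ρ = 0.2, 35.1% at 0.3, 28.7% at 0.5 and 21.3% at 0.7.
- Simulated trials (8,000) with 380 per arm, exponential death times giving 70% 3-year survival, an assumed recurrence hazard of 0.2 per year with 40% of recurrences local, and three short-term outcomes independent of the rest: 34.2% for ten tests and 25.7% for six. The six-test run used the 3-year comparisons of OS and DFS in place of log-rank tests.

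**5. Comparison.** One designated primary test has a false-positive rate of 5%. The lowest figure above, 21.3%, is a little over four times that.

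**The case against.** **The sample size already identifies the lead outcome.** This is the strongest reply, and part of it stands. A reader might infer that all outcomes have equal rank. That goes too far, because section 2.2.1 sizes the trial on 3-year survival alone. But an implied lead outcome is not a designated one. Section 2.4.2 does not separate 3-year OS from the other time points, and section 2.5 offers two tests that could apply to it.

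**The false-positive figure is not in the documents.** This stands. A reader might infer ten tests and a flat one-in-three risk. The log-rank sentence in section 2.5 supports six tests at least as well, and one in three depends on correlations that someone must assume. Nor does the text support testing the four complication types separately; they are named as what the complication rate covers. Only a range with stated assumptions is defensible.

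**The error rate presumes no true difference, while the Introduction expects differences.** This also stands. Detecting a real difference in safety or recurrence is not a false positive. Opposite expected directions are a reason to name a lead outcome; they are not evidence of inflated error. Nor does the article state any rule for declaring a winning arm.

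**This is a condensed article, and an SAP may settle multiplicity.** How secondary outcomes are ordered or adjusted can be left to an SAP, and its absence alone would be no finding. Which outcome decides the trial is not normally left there, and the article has both an outcomes section and a sample-size section. An SAP that reserved 0.05 for one test would also depart from section 2.5 as written.

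**Conclusion.** The concern holds in a limited form. The plan names no primary outcome, fixes no single test for the survival outcome behind its sample size, and applies one unadjusted .05 rule to every comparison. That much rests on the text alone.

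The size of the error depends on assumptions: no true difference on any outcome, a test count of six or ten, and correlations the documents do not give. Within those limits it is about 26% for six tests and about 21% to 40% for ten, against 5% for one primary test. Strong correlation among the six tests would lower their figure too. The lack of a fixed deciding result does not depend on any of these figures.

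The missing second survival rate in section 2.2.1 is a separate matter.

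**What to change.** Make three changes to the protocol text before any outcome data are seen, since naming a primary outcome afterwards cannot restore error control.

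1. In section 2.4, name overall survival as the sole primary outcome, in line with section 2.2.1.
2. In section 2.5, specify one test for it at two-sided 0.05 and restrict the significance rule to that test. One option is a log-rank test over follow-up to 36 months, reported with the 3-year Kaplan-Meier difference and its 95% confidence interval. A comparison of 3-year rates would match the wording of section 2.2.1 more literally. Either can serve, provided that one is chosen and the sample-size section names the same one.
3. Label 1- and 2-year OS, DFS, local recurrence, complications, AFP and hospital stay as secondary, and report them with 95% confidence intervals and without confirmatory claims.

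This is a change of wording only, with no added patients, visits or procedures. The downside is that a clear difference in, say, complications or DFS could be reported as an estimate but not claimed as a confirmed result.

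### The methods listed for the local recurrence rate either ignore censoring or, by censoring deaths, overstate recurrence; a cumulative incidence estimate would do neither (minor, cheap to improve)

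*Protocol article*

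**What the plan says.** Section 2.4.2 (Long-term outcomes) names three items: "1, 2, 3-year overall survival (OS) rates", the matching disease-free survival rates, and "Local recurrence rate". The first two have time points; local recurrence has none. The section sets visits every 3 months and closes follow-up at death or the last visit. It does not say how a patient who dies without local recurrence enters the recurrence rate.

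Section 2.5 (Statistical methods) gives a t test or Mann-Whitney test for quantitative variables. For the rest it says "A Pearson Chi-square test was applied to analyze categorical data", and it assigns Kaplan-Meier and the log-rank test to every curve. No test is tied to local recurrence by name, and no cumulative incidence or other competing-risk method appears.

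Section 2.2.1 (Sample size) supplies the two figures that bear on the point. It takes from a previous report that "the 3-Year survival rate of small HCC is 70" per cent, and it plans for loss: "Considering the withdrawal rate of 10%, the total number of patients is determined as 760, 380 in each group".

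**The concern.** Observation of local recurrence can stop in two ways before recurrence is seen: the patient is lost, or the patient dies. These need different handling. A lost patient may still recur unobserved; a patient who has died cannot.

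- **Crude proportion with chi-square.** With complete follow-up to a fixed time, this estimates the right quantity, because deaths count as not having recurred. With withdrawals it does not, because lost patients are either counted as recurrence-free or dropped.
- **Kaplan-Meier with deaths censored.** This handles withdrawal, but treats the dead as if they could still recur. One minus the estimate (1-KM) is then the recurrence risk in a hypothetical population without death, and it exceeds the proportion of patients who recur.

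The Introduction rests the comparison on ablation being safer but having higher recurrence and local progression. Local recurrence is therefore one of the figures readers will look for, and its reported percentage should mean what it appears to mean.

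**Working it through.** **Inputs from the article.** 3-year survival 70% (section 2.2.1), so 30% all-cause deaths; planned withdrawal 10% (section 2.2.1). The article states no expected recurrence rate, so there is no plan figure to reproduce. The 355 per group does not enter this calculation.

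**Assumptions (not in the article).** Constant hazards over 3 years; censoring independent of outcome; recurrence and recurrence-free death set over a range.

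**1. Overstatement by Kaplan-Meier with deaths censored.** Let 1-KM be 15% at 3 years. The cumulative recurrence hazard is Hr = -ln(0.85) = 0.1625. Let d be the 3-year risk of recurrence-free death taken on its own, so Hd = -ln(1 - d). The true cumulative incidence is

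CIF = Hr/(Hr + Hd) × [1 - exp(-(Hr + Hd))].

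| d | Hd | 1 - exp(-(Hr + Hd)) | CIF | 0.15/CIF |
|---|---|---|---|---|
| 5% | 0.0513 | 1 - 0.85×0.95 = 0.1925 | 14.6% | 1.025 |
| 10% | 0.1054 | 1 - 0.85×0.90 = 0.2350 | 14.3% | 1.05 |
| 20% | 0.2231 | 1 - 0.85×0.80 = 0.3200 | 13.5% | 1.11 |
| 30% | 0.3567 | 1 - 0.85×0.70 = 0.4050 | 12.7% | 1.18 |

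The last row is the extreme: it requires that every death behind the 70% survival figure occurs without prior local recurrence.

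**2. The same check with the true incidence fixed.** Here recurrence-free death is the proportion of all patients who die without recurrence, a slightly different scale from d. If true 3-year incidence is 20%, 1-KM gives 20.6%, 21.2%, 22.5% and 24.2% when 5%, 10%, 20% and 30% die recurrence-free. Over true incidence of 10% to 30% and recurrence-free death of 3% to 30%, the overstatement runs from 0.2 to 6.8 points (2% to 23% relative). At 5% to 10% recurrence-free death it is only 0.3 to 1.8 points.

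**3. Error of the crude proportion under 10% withdrawal.** The withdrawal hazard is Hc = -ln(0.90) = 0.1054. Take true incidence 20% and recurrence-free death 10%:

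- Total event hazard is -ln(0.70) = 0.3567, of which recurrence is 0.3567 × 20/30 = 0.2378.
- Withdrawals counted as recurrence-free: 0.2378/(0.3567 + 0.1054) × (1 - 0.70×0.90) = 0.5146 × 0.37 = 19.0%, which is 1.0 point too low.
- Withdrawals dropped: the share withdrawn is 0.1054/0.4620 × 0.37 = 8.4%, so the proportion is 0.1904/(1 - 0.0844) = 20.8%, too high by a similar amount.

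Across true incidence of 10% to 30%, counting withdrawals as recurrence-free understates by 0.5 to 1.4 points. If early censoring reached an assumed 30%, the 20% would be read as 17.0%.

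**4. Check on disease-free survival.** With death counted as an event, Kaplan-Meier in a simulation of 200,000 patients gave 69.9% against a true 70.0%, so there is no bias there.

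**The case against.** **No test is assigned to local recurrence, and a full analysis plan may specify one.** It is true that the article never says chi-square or Kaplan-Meier will be used for this outcome, and chi-square has obvious uses elsewhere (complications, adverse events, sex). What remains is that section 2.5 sends every curve to Kaplan-Meier and all categorical data to chi-square. A recurrence rate reported under that section takes one of the two routes. This supports a minor point, not a claim of stated error.

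**The bias may be small.** This stands. The 70% is all-cause survival. Only deaths without prior local recurrence compete, and the article does not give their share. A reader might take 30% as the operative figure; it is only a ceiling.

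**The fixed-time survival rates.** A reader might infer that the 1-, 2- and 3-year overall and disease-free survival rates share the problem. The article does not support that. Death is the event for overall survival and, in the usual sense of the term (the article gives no definition), part of the event for disease-free survival. Kaplan-Meier handles the censoring in both, and nothing in the article applies chi-square to them.

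**The between-arm test.** A reader might also infer that the log-rank comparison is invalid. It is not: with deaths censored it validly compares cause-specific hazards. Only the estimated probability is off. Replacing it with Gray's test would not be a clear gain, because cumulative incidence falls when early deaths rise. With the same recurrence hazard in both arms (1-KM 20%), recurrence-free death of 5% versus 15% gives cumulative incidences of 19.5% and 18.5%, so the arm with more deaths looks better.

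**Conclusion.** The point holds for the estimation of local recurrence only. Under section 2.5 the rate would be either a crude proportion that mishandles the planned withdrawals, or a Kaplan-Meier figure that overstates how many patients recur.

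At an assumed 1-KM of 15%, the relative overstatement is about 2.5% to 18% as recurrence-free death goes from 5% to the 30% ceiling. The crude proportion with withdrawals counted as recurrence-free is low by about 0.5 to 1.4 points at 10% withdrawal and assumed recurrence of 10% to 30%. All of this rests on constant hazards, independent censoring and assumed event rates. No distortion of the arm comparison by log-rank has been shown. Severity is minor: this is a cheap improvement in how one outcome is estimated.

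**What to change.** In section 2.5, state that:

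- the local recurrence rate is estimated at 1, 2 and 3 years by the cumulative incidence function, with death without local recurrence as a competing event, and reported with 95% confidence intervals;
- the arms are compared by the log-rank test already named, with a cause-specific hazard ratio;
- chi-square is not used for local recurrence;
- Kaplan-Meier remains the method for overall and disease-free survival.

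The cost is a few lines of text. No additional visits or patients are needed, provided that dates of recurrence, death and last visit are recorded at the 3-monthly visits. The one downside is that cumulative incidence may have to be run outside the named package, SPSS v22.0.
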